#### General approach

Statistical analysis will be performed using the statistical software R (www.r-project.org), version 4.1.0 or higher. Data scientists will remain blinded through the use of non-meaningful group labels, e.g., the groups will be called “group A” and “group B”. For descriptive statistics, continuous variables will be summarized using the arithmetic mean and standard deviation; in case of skewed distribution, median and interquartile range are used. Categorical variables will be summarized using total counts and percentages.

Unless otherwise stated, the estimate with the corresponding two-sided 95% confidence interval and two-sided *p*-value will be reported for all confirmatory and exploratory analyses. *P*-values less than 5% will be considered statistically significant. Details of the statistical analysis will be later specified in the statistical analysis plan (SAP).

Demographic and baseline variables will be summarized in a table, stratified by treatment and control group. Continuous variables will be summarized using the arithmetic mean and standard deviation; in case of skewed distribution, median and interquartile range are used. Categorical variables will be summarized using total counts and percentages. No inferential statistics will be used to compare baseline characteristics. Details on variables reported in this table will be defined in the SAP.

#### Primary and secondary endpoints

For the primary endpoint, the main aim is to estimate the odds ratio (OR) of DiGA use with digital nurse support vs. unsupported prescriptions. The confirmatory analysis will be conducted in the full analysis set (FAS, see below) based on the intention-to-treat (ITT) principle. The analysis of the primary endpoint is carried out using a logistic regression model. In addition to the intervention group, the model also includes age, gender, and the recruiting center as well as possible other factors as covariates. One-sided *p*-value corresponding to the hypothesis given above, estimated OR and corresponding one-sided confidence interval will be reported. One-sided *p*-value will be calculated as half of the *p*-value from the fitted model output.

Analyses of all secondary outcomes are exploratory and will be done as complete case analyses, meaning that only cases with available data for the analysis are included. Analysis of the secondary efficacy outcomes will be undertaken following the same framework as the primary outcome model, particularly using the same covariates in the models. For each continuous outcome including the PHQ-9 and SUS, a linear regression model will be fitted. For the analysis of PHQ-9, the baseline value is included in the model as an additional covariate. The estimates for the group effect with accompanying 95% confidence intervals and two-sided *p*-values will be reported. Details of the models will be specified in the statistical analysis plan (SAP).

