## Assignment of interventions: blinding

### Who will be blinded {17a}

It is not feasible nor possible for the participating patients and most project staff to be blinded to treatment allocation. Primary outcome assessment will be based on patient report, blinding is not possible. Staff who analyze the data will be blinded (arms will be designated randomly at that point as A and B). Data review will be performed blinded.

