## Statistical methods

### Statistical methods for primary and secondary outcomes {20a}

We assume that the additional support from a digital nurse will lead to a greater proportion of older patients using the DiGA compared to support from an explain film alone.

Since this is a feasibility and proof-of-concept study, the main hypothesis will be tested one-sided at a significance level of 5%, i.e., the null hypothesis “smaller or equal frequency of use in the intervention group compared to the control group” vs. the alternative hypothesis “greater frequency of use in the intervention group compared to the control group” will be tested, i.e., the following null and alternative hypothesis will be tested:$$H_0:p_I\leq p_{K\;}vs.\;H_1:p_I>p_K.$$

Here, $${p}_{I}$$ and $${p}_{K}$$ stand for the frequency of DiGA use in the intervention (digital nurse) and control group, respectively.

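### The rule for the confirmatory one-sided p-value halves the model p-value without a condition on direction, so it gives the wrong number whenever the estimated OR is below 1

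*Protocol article*

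**What the plan says.** All references are to the protocol article.

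- *Statistical methods for primary and secondary outcomes {20a}*: "the main hypothesis will be tested one-sided at a significance level of 5" per cent. The null hypothesis is p_I ≤ p_K, and the alternative is "greater frequency of use in the intervention group compared to the control group".
- *Primary and secondary endpoints*: "The analysis of the primary endpoint is carried out using a logistic regression model". The target is the odds ratio for nurse support against unsupported prescription. Then: "One-sided *p*-value corresponding to the hypothesis given above, estimated OR and corresponding one-sided confidence interval will be reported". The next sentence gives the computation: "One-sided *p*-value will be calculated as half of the *p*-value from the fitted model output".
- *General approach*: p-"values less than 5% will be considered statistically significant", and "Data scientists will remain blinded through the use of non-meaningful group labels". *Who will be blinded {17a}* says the same of the analysts, with arms called A and B.

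**The concern.** The usual p-value for a coefficient in a logistic regression is two-sided, so it is the same for an effect of given size in either direction. Halving it gives a one-sided p-value for whichever direction the data happened to take. That is the p-value for the stated alternative only when the estimate favours the nurse arm. The halving sentence carries no such condition.

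The sentence governs the trial's only confirmatory p-value. Followed to the letter, it would return a value below 5% when nurse support significantly lowers use. That value would stand beside a one-sided confidence interval that does not exclude an odds ratio of 1 in the favourable direction, and the article does not say which of the two decides. Neutral labels add a practical wrinkle: p/2 can be computed without knowing which label is the nurse arm, whereas the correct one-sided p-value cannot.

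**Working it through.** **Inputs.** One-sided 5% level and H1: p_I > p_K (section {20a}); logistic regression and the halving rule (*Primary and secondary endpoints*); 30% use under control, 50% with support, 84 per group, 100 per group after about 15% drop-out (*Sample size {14}*). The calculations use the Wald p-value, the default in R logistic regression output; this is an assumption, as the article does not name the test.

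**1. The plan's own sample size.** Exact power of the one-sided Fisher test at 30% vs 50%, by enumeration, is 0.798 at 83 per group and 0.805 at 84. So 84 is reproduced. With drop-out, 84 / 0.85 = 98.8, hence 99, rounded to 100. The planned test is properly one-sided at this stage.

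**2. The two formulas.** Let z be the statistic for log OR (intervention vs control) and p = 2[1 − Φ(|z|)] the two-sided p-value. The one-sided p-value for H1 is 1 − Φ(z), which equals
- p/2 if OR > 1,
- 1 − p/2 if OR < 1.

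The article's rule is p/2 in both cases.

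**3. One table with the effect in the wrong direction (counts assumed for illustration).** Nurse 15/100, control 30/100.
- log OR = ln(15/85) − ln(30/70) = −1.7346 + 0.8473 = −0.887; OR = 0.41.
- SE = √(1/15 + 1/85 + 1/30 + 1/70) = √0.1261 = 0.355.
- z = −0.887/0.355 = −2.50; two-sided p = 0.0124.
- Article's rule: p/2 = 0.006, below 5%.
- Correct one-sided value: 1 − 0.006 = 0.994.
- One-sided lower 95% limit for the OR: exp(−0.887 − 1.645 × 0.355) = 0.23, far below 1.

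The p-value and the interval point to opposite conclusions.

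**4. Rejection rates under equal true rates.** All 2×2 tables were enumerated for the unadjusted model. Mechanical halving rejects when |z| > 1.645; the directional rule rejects when z > 1.645.

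| n per arm | true rate, both arms | mechanical halving | of which OR > 1 (= directional rule) | of which OR < 1 |
|---|---|---|---|---|
| 100 | 30% | 0.1007 | 0.0504 | 0.0504 |
| 100 | 40% | 0.0973 | 0.0486 | 0.0486 |
| 100 | 50% | 0.1036 | 0.0518 | 0.0518 |
| 84 | 30% | 0.0986 | 0.0493 | 0.0493 |
| 84 | 40% | 0.0983 | 0.0491 | 0.0491 |
| 84 | 50% | 0.1049 | 0.0525 | 0.0525 |

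A simulation of 4,000 trials with adjustment for age, sex and four centers (covariate effects assumed) gave 0.107 for mechanical halving and 0.0535 for the directional rule.

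**5. Under the design assumption.** At 30% vs 50% the rejection rate of this test is 0.895 (100 per arm) or 0.845 (84 per arm) under either rule, because significant results in the wrong direction have probability of about zero. Power is unchanged.

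**The case against.** The strongest reply is that the halving sentence should not be read alone. The sentence before it defines the p-value as the one that belongs to the stated hypothesis, the hypothesis is given in words and symbols, and the odds ratio is oriented as nurse against unsupported. On that reading, halving is shorthand for a quantity already defined as directional, and the reported OR and interval would expose a result in the wrong direction. This stands, and it limits the point: a careful analyst would not claim superiority with an OR below 1. It does not make the sentence correct. The article could have left the computation to the SAP; it fixed it instead, and the rule is wrong for half of the possible signs of the estimate.

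A reader might go further and infer that the plan has no check on direction and that its actual type I error is 10%. The documents do not support this. That figure requires someone to apply the halving mechanically and to disregard the OR and the interval.

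A reader might also infer that blinding makes it impossible to check direction. That is not stated either. The nurse-vs-control OR and its one-sided interval cannot be produced until the labels are mapped, so mapping must happen at some point; the article only leaves open when.

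Finally, high rates of false superiority can be computed for a harmful intervention: about 50% if support lowered use from 30% to 20%, with 100 per arm. No section gives such a rate. It is an assumed scenario and should carry little weight.

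**Conclusion.** The point holds as a small error in the stated computing rule. The rule is right if the estimated OR is above 1, as the investigators expect, and wrong otherwise. Its consequence, if applied mechanically, is a rejection rate of about 10% under equal true rates (0.097 to 0.105 across the settings enumerated; 0.107 in the adjusted simulation) against the stated 5%, with half of those rejections in the wrong direction. With the direction respected, the rate is about 5%. These figures rest on a Wald test, complete data and true rates of 30% to 50%. Since the article fixes a directional hypothesis and reports the OR and a matching interval, the type I error actually intended remains 5%, and a false claim of superiority is unlikely.

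**What to change.** Replace the halving sentence with: *The one-sided p-value is half of the two-sided model p-value if the estimated OR (intervention vs control) is above 1, and 1 minus half of it otherwise.* Add that labels A and B are mapped to intervention and control before the one-sided p-value and the one-sided confidence limit are produced.

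This wording is preferable to a formula based on a normal statistic. Missing primary endpoint values are to be imputed, with details left to the SAP, and pooled inference after multiple imputation may use a different reference distribution. The conditional rule works with whichever two-sided p-value the final model yields.

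The cost is two sentences in the protocol or SAP and one line of code. Conduct, sample size and power do not change.

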### Outcomes {12}

The primary endpoint is DiGA use at week eight after randomization (yes/no). It is recorded whether the patients have started using the DiGA within 8 weeks, i.e., whether they have started at least the first online session. We chose an intervention period of 8 weeks because administrative processes such as request to the health insurance companies, and the installation/navigation to the website may last several weeks until the first use of the DiGA is possible at all.

Secondary endpoints are DiGA use after 16 weeks, change in depressive symptoms (measured by PHQ-9 [26]), and change in treatment of mental disorder after 8 and 16 weeks. The usability of the DiGA will be assessed by the System Usability Scale (SUS) [27] and the User Experience Questionnaire (UEQ) [28] at week eight and 16.

All outcomes will be assessed via personal/telephone interviews and patient self-report.

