### Sample size {14}

The sample size to test the main hypothesis was calculated using a Fisher’s exact test at a one-sided significance level of 5% and to achieve a power of 80%. It was assumed that under control 30% of the participants would start using DiGA and that this proportion would be increased to 50% through the support of the digital nurse. This resulted in a required number of cases of 84 patients per group. Due to a possible drop-out (assumption approx. 15%), 100 patients per group should be included in the study.

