#### Safety analysis dataset

The safety analysis set will include all randomized patients.

Missing values of the primary endpoint will be imputed. Details of the model, imputation of missing values and sensitivity analysis will be specified in the SAP.

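### Complete-case analysis leaves collected week-8 PHQ-9 scores, and possibly known week-8 DiGA starts, out of the week-16 analyses; a repeated-measures model and a stated week-16 definition would use them

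*Protocol article*

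**What the plan says.** In the protocol article, Primary and secondary endpoints {20a} states that "Analyses of all secondary outcomes are exploratory and will be done as complete case analyses", and explains this as "meaning that only cases with available data for the analysis are included". For PHQ-9 the model is named: "For each continuous outcome including the PHQ-9 and SUS, a linear regression model will be fitted", and "For the analysis of PHQ-9, the baseline value is included in the model as an additional covariate". The other covariates are those of the primary model.

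The only imputation commitment is in {20c}: "Missing values of the primary endpoint will be imputed". The SAP is left to supply model details, the imputation method and sensitivity analyses.

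Outcomes {12} makes DiGA use by week 8 the primary endpoint, defined as having started at least the first online session. DiGA use after 16 weeks and PHQ-9 change at weeks 8 and 16 are secondary. The definition of use is not repeated for week 16.

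Methods for additional analyses {20b} names the observed PHQ-9 difference as one of three considerations for the feasibility of a multi-center trial.

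**The concern.** Complete case is a method the protocol has chosen, not a detail left to the SAP. Two consequences follow at week 16.

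**PHQ-9.** A regression of the week-16 score on arm, baseline and the primary covariates has no place for the week-8 score, so a patient seen at week 8 and lost by week 16 drops out. Such a regression is unbiased if drop-out depends only on variables in the model. It is not protected if drop-out depends on week-8 mood in a way that differs by arm. The design makes that possible: the trial is open-label {17a}, outcomes are self-reported {12}, and only the intervention arm has a digital nurse, who stays available until week 16 {11a}. At stake is an estimate that the protocol says it will use to judge feasibility.

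**DiGA use.** Starting a first session cannot be undone. If week-16 use keeps the week-8 definition, a patient who reported starting by week 8 has a known week-16 value. Dropping that patient because the week-16 contact failed discards an outcome already in hand.

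**Working it through.** **The plan's own figures.** The documents give no figure for this point. The related one is the sample size. A one-sided 5% Fisher's exact test of 30% against 50% has 79.8% power at 83 per group and 80.5% at 84, so 84 reproduces; 84/0.85 = 98.8, consistent with 100 per group. The 15% below is that drop-out allowance, used as an assumed week-16 missing rate.

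**1. Known starters at risk of exclusion.** With the protocol's 30% and 50% as week-8 use, and 15% lost at random by week 16:
- control: 100 × 0.30 × 0.15 = 4.5 known starters per 100
- intervention: 100 × 0.50 × 0.15 = 7.5 known starters per 100

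**2. Week-16 use rates and odds ratio.** Assumed true week-16 use is 35% and 55%, so the true OR = (0.55/0.45)/(0.35/0.65) = 2.27.

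(a) *Loss depends only on week-16 use, equally in both arms.* Let 15% of controls be missing, 10% of them starters. Then 0.015/0.35 = 4.3% of users and 0.135/0.65 = 20.8% of non-users are lost. Complete-case control rate: (0.35 − 0.015)/0.85 = 39.4%. The same loss rates in the intervention arm give 59.6%. The OR stays at 2.27.

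(b) *Loss depends on week-8 use: 5% of users and 25% of non-users, both arms.*
- control: (0.30 × 0.95 + 0.05 × 0.75)/(0.30 × 0.95 + 0.70 × 0.75) = 0.3225/0.81 = 39.8%
- intervention: (0.50 × 0.95 + 0.05 × 0.75)/(0.50 × 0.95 + 0.50 × 0.75) = 0.5125/0.85 = 60.3%
- OR = 2.30

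(c) *Pattern (b) in control only, 10% lost at random in the intervention arm.* 39.8% against 55.0%; OR = 1.85.

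The rates move by about 5 points in (a) and (b) while the OR hardly moves. The OR is materially wrong only in (c).

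**3. Week-16 PHQ-9 simulation.** The protocol gives no PHQ-9 SD or correlations, so every input is an assumption: 100 per arm, 3,000 runs, SD 5, true difference −1.5 at both visits, correlation with baseline 0.5, week 8 to week 16 correlation 0.6 or 0.75, week 8 complete. The log-odds of a missing week-16 score are set to 15% or 25% at an average week-8 score and change by 0, 0.7 or 1.0 per SD of the week-8 score. Age, gender and center are left out.

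- Complete case: the arm coefficient *b* from Y16 = *a* + *b*·arm + *c*·Y0, fitted to patients with Y16.
- Likelihood estimate using week 8: fit Y16 on arm, Y0 and Y8 in patients with Y16 (coefficients *b₂* for arm, *d* for Y8); fit Y8 on arm and Y0 in everyone (arm coefficient *b₈*); the estimate is *b₂* + *d*·*b₈*.

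| Drop-out and week-8 PHQ-9 | Complete-case bias (points) | Bias using week 8 |
|---|---|---|
| Unrelated | none beyond simulation error; variance 4–15% larger | none beyond simulation error |
| Same dependence in both arms | 0.03 to 0.07 | within 0.03 |
| Opposite directions, about 15% missing | −0.36 to −0.75 | within 0.03 |
| Opposite directions, about 25% missing | −0.59 to −1.12 | within 0.03 |

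At about 15% missing the complete-case estimate has a standard deviation near 0.67, so the bias is 0.361/0.671 = 0.54 to 0.753/0.659 = 1.14 standard errors. The bias is roughly the difference between the shifts in the two arms, so dependence in one arm only should give about half as much: 0.18 to 0.38 points, with the sign set by the arm affected.

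**The case against.** The other side has a good case. Secondary outcomes are labelled exploratory, and imputing a confirmatory endpoint while using available data for the rest is a common and deliberate distinction. The feasibility judgement has no PHQ-9 threshold. Sections {11b} and {18b} try to limit missing data by collecting outcomes at discontinuation and by repeated contact attempts. The 15% is an allowance for the primary sample size, not a week-16 forecast. A known week-8 start could be counted as available data, and that derivation rule may properly sit in the SAP. The larger PHQ-9 bias needs drop-out that differs by arm, which the documents do not show. All of this stands, and it limits the severity.

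Four stronger readings are tempting and not supported:
- *The treatment effect on DiGA use is biased because non-responders tend to be non-users.* The secondary models follow the primary framework, which targets the odds ratio; case (a) leaves it unchanged.
- *Week-8 and week-16 rates cannot be compared.* No section plans that comparison.
- *PHQ-9 analyses in general discard week-8 data.* The week-8 analysis keeps everyone with a week-8 score.
- *Known starters are certain to be dropped.* This depends on what week-16 use means, and the article does not restate it.

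The objection does not remove the main point: the named week-16 PHQ-9 model cannot use scores already collected, and the exploratory label does not protect an estimate that feeds a stated judgement.

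**Conclusion.** The point holds in limited form, with minor to moderate severity. The week-16 PHQ-9 difference is exposed to a plausible but undocumented bias. On assumed inputs it ranges from negligible (equal patterns in both arms) to about one standard error (opposite patterns, 15% missing). With random drop-out the loss is modest precision only. An analysis that uses week 8 removes this bias when drop-out depends on observed scores, and cost essentially no precision in any scenario tried.

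For week-16 DiGA use, complete case may exclude patients whose outcome is known, about 4.5 and 7.5 per 100 under random 15% loss, provided use still means first session started. Outcome-dependent loss inflates the reported rates; the odds ratio suffers only if the loss also differs by arm. The primary endpoint, its conclusion and the sample size are untouched.

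**What to change.** 1. **PHQ-9:** in the full analysis set, fit one mixed model for repeated measures to the week-8 and week-16 scores, with arm by visit, baseline PHQ-9 and the primary covariates, and report the arm difference at each visit. Patients with either score then contribute.
2. **Week-16 DiGA use:** state that it means ever started. Set it to yes for anyone known to have started by week 8, impute the remainder with the primary endpoint's imputation model, and analyse the full analysis set. Using all randomised patients instead would depart from the protocol's definition, which excludes patients who fail the eligibility criteria.
3. **Sensitivity:** keep the complete-case analyses in that role.

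The cost is a change of wording in {20a} and the SAP and a few lines of R, settled before database lock. No new data are needed. The price is slightly more analysis work and reliance on a missing-at-random assumption, which should be stated with the results.

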## Assignment of interventions: allocation

### Sequence generation {16a}

To guarantee adequate sequence generation and allocation concealment, centralized online randomization with 1:1 allocation to intervention or control group is done through REDCap. Permuted blocks of random length are used and are stratified by the center to guarantee nearly equal group size within each center.

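### The planned between-arm regression of SUS conditions on having used the DiGA, which is the primary endpoint, so its group effect cannot be read as an effect of nurse support on usability

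*Protocol article*

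**What the plan says.** The Outcomes {12} section lists the instruments at weeks 8 and 16: "The usability of the DiGA will be assessed by the System Usability Scale (SUS"), together with the User Experience Questionnaire (UEQ). The same section defines the primary endpoint as having started at least the first online session within 8 weeks.

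Under Primary and secondary endpoints {20a}, all secondary analyses are exploratory and complete-case, so that "only cases with available data for the analysis are included". The model is then fixed: "For each continuous outcome including the PHQ-9 and SUS, a linear regression model will be fitted". It uses the covariates of the primary model (age, gender, recruiting center and possible other factors). The group effect is reported with a 95% confidence interval and a two-sided p-value.

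The Sample size {14} section assumes that "under control 30% of the participants would start using DiGA and that this proportion would be increased to 50" per cent with the digital nurse.

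The article does not say who completes the SUS or UEQ. It neither describes the SUS comparison as one among users nor calls it descriptive. The assessment schedule is a figure that is not available here.

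**The concern.** The PHQ-9 and the SUS are put through the same model, but they differ in one important respect. Every randomised patient can answer the PHQ-9. A patient who never opened the DiGA has no experience from which to rate its usability. A complete-case SUS model is therefore in effect restricted to starters, and starting is what the nurse is meant to change.

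Randomisation makes the two full arms comparable. It does not make control starters comparable with nurse-arm starters. On the trial's own rationale, control starters got through insurance request, activation and first login alone, whereas nurse-arm starters should include patients who were helped past those steps. Even if the nurse changes nobody's opinion of the DiGA, mean ratings among starters can differ between arms.

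Usability is a named secondary endpoint in a trial that is meant to yield best-practice guidelines. A difference in either direction, printed with an interval and a p-value, could be taken as evidence about what nurse support does to usability.

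**Working it through.** **1. The plan's own figure.** Inputs from Sample size {14}: Fisher's exact test, "one-sided significance level of 5% and to achieve a power of 80" per cent, rates 30% and 50%, stated result "required number of cases of 84 patients per group". Full enumeration of the one-sided exact test gives power 79.8% at n = 83 and 80.5% at n = 84, so 84 reproduces. For dropout, 84 / 0.85 = 98.8, rounded up to 99, which agrees with the planned 100 per group. No sample size or power is given for the SUS.

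**2. How many patients could rate the DiGA.** Expected starters = start rate × n per arm, with "centralized online randomization with 1:1 allocation to intervention or control group".

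| n per arm | Control (30%) | Nurse arm (50%) |
|---|---|---|
| 84 | 25.2 | 42 |
| 100 | 30 | 50 |

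So about 70% of controls and 50% of nurse-arm patients would have nothing to rate at week 8. The week 16 shares are not stated.

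**3. Illustration A: logistic selection, no true effect on ratings.** These inputs are assumptions, not document figures: starting depends on a standardised literacy score with log-odds 0.8 per SD in control; the slope in the nurse arm is unchanged (0.8), halved (0.4) or zero; SUS SD 18; SUS–literacy correlation 0.3 to 0.5. Intercepts are set to give 30% and 50% starters.

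Mean literacy of starters is 0.50 SD in control, against 0.35, 0.19 or 0.00 SD in the nurse arm.

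Spurious SUS difference (nurse minus control) = difference in mean literacy × 18 × correlation:
- smallest: (0.35 − 0.50) × 18 × 0.3 = −0.8 points
- largest: (0.00 − 0.50) × 18 × 0.5 = −4.5 points

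Letting the control slope range from 0.5 to 1.2 per SD widens this to −0.5 (slope 0.5, unchanged, correlation 0.3) and −6.0 (slope 1.2, removed, correlation 0.5).

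**4. Illustration B: threshold selection.** Suppose the most apt 30% or 50% start. Mean aptitude of starters is φ(c)/f, where f is the share starting and c the matching normal cut-off: 1.159 SD at 30% and 0.798 SD at 50%, a difference of −0.361 SD. With an assumed SUS SD of 20 and correlation ρ, the spurious difference is −0.361 × 20 × ρ:
- ρ = 0.1: −0.7 points
- ρ = 0.3: −2.2 points
- ρ = 0.5: −3.6 points
- ρ = 0.6: −4.3 points

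With 25 against 42 raters, the two-sided 5% test rejects about 5.2% of the time at ρ = 0.1 and about 17% at ρ = 0.6, although there is no effect on ratings.

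**5. Scale against sampling error.** With SD 18, SE = 18 × √(1/25.2 + 1/42) = 4.5 points, or 18 × √(1/30 + 1/50) = 4.2 points. The 95% interval half-width is about 8 to 9 points. The range −0.8 to −4.5 is then about 0.2 to 1.1 standard errors, and the extreme −6.0 about 1.3 to 1.4.

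**6. Adjustment.** Illustrations A and B are unadjusted. The Background section calls higher age a decisive predictor of low digital health literacy, so the age covariate would absorb part of any literacy imbalance. Media affinity, eHealth literacy and cognitive function are listed under {20b} as possible moderators of DiGA use, but they are not among the covariates named for the model.

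**The case against.** **That only starters rate the DiGA is nowhere stated.** This is correct, and the point should say so. It does not rescue the contrast. If non-starters were also asked, their scores would not reflect use, and a comparison in which half or more of the potential respondents had never used the product would still not measure its usability.

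**A reader might infer that the SUS result is biased against the nurse arm.** The documents do not support that. The negative sign needs digital literacy to drive starting and also to raise SUS ratings. The article offers support for the first link and none for the second. Every magnitude above rests on assumed slopes, SDs and correlations. They are unadjusted, and the phrase about possible other factors leaves room for the SAP to add eHealth literacy or media affinity. This objection stands: what can be claimed is that the contrast is not interpretable as an effect on usability, not that it leans a known way.

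**The bias may be small beside the noise.** Also fair. Over most of the illustrated range it is about one standard error or less, and at the low end the false-positive rate is close to nominal. A wide interval does not, however, change what is being estimated.

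**It is exploratory and the SAP will give details.** The first part limits the consequence: the primary conclusion is untouched, and the SUS is not among the feasibility criteria listed under {20b}. The second does not dispose of the point, because the article already fixes the population, the model and the reported estimate for the SUS. This is a choice already made, not a detail left open.

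**Conclusion.** The point holds in a limited form. The article commits to a between-arm SUS regression on available cases with an interval and a p-value. On the trial's planned rates, that compares about 25–30 control raters with 42–50 nurse-arm raters, selected through the primary endpoint itself. The resulting group effect cannot be read as an effect of nurse support on usability. The same applies to the UEQ, which also rates the DiGA.

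This rests on one inference, that a meaningful rating needs use, and on the protocol's 30% and 50%. The size and sign of any bias are not determined by the documents. The range of about −0.5 to −6 points is illustrative, unadjusted and conditional on literacy driving both starting and ratings; age adjustment would reduce it. The PHQ-9 is not affected in this way, and neither is the primary analysis. It is worth correcting because the change is nearly free, but it does not threaten the trial's main result.

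**What to change.** Take the SUS and UEQ out of the group-effect regression. Report them descriptively among starters, by arm and time point, with the number of starters and the number of raters, without a p-value, and with a label saying that the summary is conditional on having used the DiGA. State in the SAP who is asked to complete the two instruments.

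An analysis of all randomised patients that ranks non-starters lowest should be optional only. It would tie about 70% of controls and 50% of nurse-arm patients at the bottom and so largely retest the primary endpoint. If it is done, it should be labelled as a composite dominated by DiGA start.

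The cost is a change of wording and the loss of an exploratory p-value. Data collection and sample size stay as they are.
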